## Abstract

**Background:**

Ostomy surgeries involving the placement of an ostomy bag (eg, colostomy, ileostomy, urostomy, etc) have been shown to have a negative impact on health-related quality of life. To date, no studies have been conducted examining what impact, if any, wearable biosensors have on the health-related quality of life of ostomy patients.

**Objective:**

In the present study, we plan to assess the quality of life of ostomy patients using the Ostom-i alert sensor, a portable, wearable, Bluetooth-linked biosensor that facilitates easier ostomy bag output measurements. We hypothesize that using the Ostom-i alert sensor will result in an improved, ostomy-specific, health-related quality of life as compared to baseline measurement before the use of the sensor.

**Methods:**

A total of 20 ostomy patients will be screened and recruited to participate in this prospective, observational, cross-over pilot study using an Ostom-i alert sensor for one month. The primary outcome of this study will compare ostomy-specific, health-related quality of life at baseline (prior to Ostom-i alert sensor use) to ostomy-specific, health-related quality of life after 2 and 4 weeks of Ostom-i use by utilizing the City of Hope Quality of Life Questionnaire for Patients with an Ostomy. Secondary outcomes of general health-related quality of life and adjustment to ostomy will be evaluated using the Medical Outcomes Study 36-item short form health survey and the Olbrisch Ostomy Adjustment Scale Short Form 2.

**Conclusions:**

Proposed benefits of mobile, internet-linked personal health monitors, such as the Ostom-i, include a reduction in the cost of care by reducing resource utilization and infection rates, improving patient-provider communication, reducing time spent as an inpatient as well as improved quality of life. Prior studies have demonstrated decreased health-related quality of life in patients with an ostomy bag. We aim to examine the extent to which the Ostom-i alert sensor affects the health-related quality of life of its users. The Ostom-i alert sensor has the potential to improve quality of life of users by giving them the freedom and confidence to partake in daily activities with the knowledge that they can check how full their ostomy bag is in a private, discrete manner.

**Trial Registration:**

ClinicalTrials.gov NCT02319434; https://clinicaltrials.gov/ct2/show/NCT02319434 (Archived at WebCite at http://www.webcitation.org/6xhFDThmq)

## Introduction

### Background and Rationale

Ostomy surgeries such as colostomy (large bowel), ileostomy (small bowel), and urostomy (bladder), which require the use of an ostomy bag either temporarily or permanently, may result in a change in health-related quality of life as patients adjust to life with their ostomy [1-4]. While the average wear time of an ostomy bag in the United States has been reported to be 4.8 days, up to 40%-60% of stoma will never be reversed and many patients with severe inflammatory bowel disease or advanced colorectal cancer may wear an ostomy bag long-term [5-7]. Colostomies requiring an ostomy bag are common in patients with colorectal cancer, which as of 2016 was the second most commonly diagnosed cancer in men and the third most commonly diagnosed cancer in women in the United States [8]. In 2016, the number of newly diagnosed cases of colorectal cancer was 724,690 and 727,350 in men and women, respectively. Estimates suggest that there will be 910,190 newly diagnosed cases of colorectal cancer in men and 885,940 new cases in women in 2026. It has been reported that colostomy surgery is more common in patients with rectal cancer (29%) than for patients with colon cancer (12%) [8].

While ostomy surgery may improve health-related quality of life by reducing disease burden, it can often decrease general quality of life in other ways. Common themes in health-related quality of life for ostomy patients include factors such as social adjustment, fatigue, pain, leakage, physical functioning, changes in clothing, and diet [9]. A significant concern of patients with an ostomy bag is return to work, work efficiency, and worries about social and personal life due to the presence of the ostomy bag [10]. While factors such as coping, acceptance, and availability of ostomy specialist to patients have been identified as methods to improve health-related quality of life of ostomy patients, there have been few technological advancements geared towards improving health-related quality of life of individuals with an ostomy bag [11,12]. Existing portable technologies are primarily focused on the cleaning of the ostomy bag, such as a 2004 patent allowing the user to clean the bag more completely and with greater ease; however, no mobile health (mHealth) technologies currently exist to alert the wearer as to the fullness of their ostomy bag [13].

We are conducting a prospective trial to evaluate the impact of the Ostom-i alert sensor on short-term, health-related quality of life of ostomy patients. The Ostom-i alert sensor is a wearable device intended to make life easier for patients with ostomy bags by allowing for easier output measurements and anticipation of bag changes via a Bluetooth connection to their mobile smart phone. Using the City of Hope Quality of Life Questionnaire for a Patient with an Ostomy (CoH-QOL-Ostomy), we determine to what extent, if any, the Ostom-i sensor affects health-related quality of life of the user [14].

### Objective

We hypothesize that using the Ostom-i alert sensor will result in an improved ostomy-specific, health-related quality of life as compared to baseline measurement before the use of the sensor. We intend to assess the change in ostomy-specific health-related quality of life, with the Ostom-i alert sensor. We will use the City of Hope Quality of Life Questionnaire for Patients with an Ostomy. Secondarily, we aim to measure the change in general health-related quality of life and ostomy adjustment using the Medical Outcomes Study 36-item short form health survey (SF-36) and the Olbrisch Ostomy Adjustment Scale Short Form 2 (OAS-SF2), respectively [15,16].

## Methods

### Participants, Interventions, and Outcomes

#### Study Setting

Patient recruitment will occur at the Stanford University Medical Center. Data analysis and all other matters related to manuscript drafting will occur at the Stanford University School of Medicine. Both settings are located in Palo Alto, California within Santa Clara County.

#### Eligibility Criteria

Recruited patients will be required to meet the eligibility criteria outlined in Textbox 1. Any participants who do not meet our inclusion criteria will be excluded from the study. Our decision to exclude participants who have had an ostomy for less than 6 months was based off the work of Husain and Cataldo [6], who determined that 93% of ostomy-related complications occur within the first six months after ostomy surgery. Furthermore, they determined that psychological adjustment to the ostomy occurs 6 to 10 weeks after surgery, implying that participants in our population will be fully psychologically adjusted to their ostomy [6]. We are limiting our study to patients with colostomy, ileostomy or urostomy. Large urostomy bags will not work with the Ostom-i sensor and thus individuals with large urostomy bags (>9 cm) will be excluded from the study (see Textbox 1 for a complete list of patient inclusion and exclusion criteria).

#### Recruitment

Participants will be recruited from the Stanford University Medical Center via word of mouth, online advertisements, flyers posted in the hospital as well as referrals from ostomy physicians and nursing staff. Patient recruitment will be facilitated with the help of a number of ostomy nurses at Stanford. Persons interested in the study will be directed to a Web page which includes information about the study sensor, what study participation involves, and a link to a complete online eligibility survey. Participants will not receive monetary compensation for participating in this study, but will be able to keep the Ostom-i sensor which retails for US $125.

Study eligibility inclusion and exclusion criteria.
**Inclusion Criteria**
Ability to read and understand English18-80 years of ageCurrent use of an ostomy bagUse of an ostomy bag for 6 months or moreUse of an ostomy bag for the duration of the studyAccess to and ability to use an iOS or Android smartphone, iPod Touch or tablet
**Exclusion Criteria**
Ostomy bag other than colostomy, ileostomy or urostomyUrostomy bag larger than 9 cm

#### Screening

Participant screening will occur either online via the Web page, in person, or over the phone. The online screening survey will use Stanford Medicine Qualtrics to collect and analyze data on eligible persons [17].

#### Randomization

Patients will serve in both the control and interventional arms of this cross-over pilot study. A cross-over design is advantageous for this pilot study as it allows patients to serve as their own control, therefore variances attributable to confounding factors [18,19]. Once eligibility is confirmed, consent will be obtained and the baseline survey will be given (CoH-QOL-Ostomy, SF-36 and OAS-SF2). After completion of the baseline survey, the participant will be given their Ostom-i alert sensor along with a video tutorial which explains how to use the device.

#### Intervention

Once completing the baseline survey, patients will enter the intervention arm of the study where they will receive an Ostom-i sensor which they will use over the course of 4 weeks. Two and 4 weeks after receiving the sensor, primary and secondary outcome measures will be assessed. The Ostom-i is a flexible, Bluetooth-linked sensor that attaches to the patient’s ostomy bag. The sensor portion of the Ostom-i device is a flexible potentiometer produced by Spectra Symbol [20]. The sensor determines the level of the ostomy bag based on the angle of flex it experiences and automatically adjusts when the user is laying down or standing up. The sensor can be adjusted in size from 7 cm to 9 cm to fit a variety of ostomy bag sizes. Data collected by the sensor is sent via Bluetooth to the user’s iOS or Android device and provides alerts informing the wearer of the level of their ostomy bag (Figure 1 and 2).

#### Participant Timeline

Participants will retake all 3 surveys after 2 and 4 weeks of device use as previous validation studies of these surveys have used 2-4 week intervals [16,21]. Following completion of the week 4, survey participant involvement in the study will end (see Figure 3 for the study flowchart). Participants will have the option to take the week 2 and week 4 surveys either in person at the hospital or at home, using a paper-based or online format.

#### Primary Outcome Measures

The modified CoH-QOL-Ostomy is an ostomy-specific, health-related quality of life instrument with four dimensions. The four dimensions—physical, psychological, social, and spiritual well-being are defined in Table 1. Ostomy-specific, health-related quality of life is calculated by summing scores for each question then dividing by the total number of questions (ie, 43 questions). Total scores for each of the four dimensions are calculated by adding scores on all dimension items and dividing by total number of dimension items. Ostomy-specific, health-related quality of life will be measured at baseline prior to receiving the Ostom-i device, then again after 2 and 4 weeks of device use.

#### Secondary Outcome Measures

Two secondary outcome measures will be utilized including the SF-36 and the OAS-SF2. The SF-36 is a commonly used general health-related quality of life instrument. In this study, it will be used to compare ostomy-specific, health related quality of life to general (nonostomy-specific) health-related quality of life. The OAS-SF2 is used to examine subjective response to ostomy as well as psychological adjustment to the ostomy.

#### Null Hypothesis and Sample Size

Our null hypothesis states that there will be no improvement in ostomy-specific, health-related quality of life as measured by the CoH-QOL-Ostomy, compared to baseline measurements prior to sensor use. To calculate the desired sample size to test our null hypothesis, the following paired *t*-test formula was used:

*n=[σ_d_^2^(Z_power_+Z_α/2_)^2^]/μ_d_^2^*

where our mean and variance is based on the work of Gemmill et al [22], who examined 307 ostomy patients and reported a mean of 8.0 (SD 1.7) for the social well-being dimension within the CoH-QOL-Ostomy, with 80% power and 95% confidence [22]. Our sample size calculation (n=16 for a 15% difference in the dimension of social well-being) was again based on Gemmill et al [22], who reported social well-being to have a higher mean (8.0) than overall quality of life (mean 7.7).

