**Figure 3 figure3:**
[figure not shown]
Participant flowchart. QOL-Ostomy: Quality of Life Questionnaire for a Patient with an Ostomy.

**Table 1 table1:** City of Hope quality of life dimension definitions obtained from Gemmill et al [22].

Dimension	Definition
Physical well-being	Physical symptoms and functional ability
Psychological well-being	Emotional components of the illness including positive as well as negative aspects
Social well-being	Role of the patient with the family and society including occupational, sexual, and personal relationships
Spiritual well-being	Religious aspects and existential concerns

**Table 2 table2:** Desired sample size number (N) based on % difference.

% Difference	Absolute change in dimension of well-being (μd)	Sample size (N)
10	0.8	35
15	1.2	16
30	2.4	4
40	3.2	2

Furthermore, Gemmill et al [22] report a lower SD for the dimension of social well-being (SD 1.7) as compared to physical well-being (SD 1.8), psychological well-being (SD 1.9), and spiritual well-being (SD 2.3). Thus, we chose to base our sample size calculation on the dimension of social well-being. With a sample size calculation of n=4 for 30% difference, we are concerned that our results would lack generalizability. Therefore, by increasing our sample size to 20, we hope that our results will be more generalizable and may help account for a potential 20% attrition rate during recruitment (Table 2).

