#### Statistical Analysis

Data will be presented as mean (SD). Changes between pre- and postintervention quality of life will be assessed using a dependent participant’s paired *t*-test with 95% confidence interval. Depending on participant retention throughout the course of the study, we may choose to use mixed model regression analysis which would allow us to incorporate incomplete data sets from participants who might not complete the study. Furthermore, we also may choose to use repeated measures analysis of variance to examine differences in population mean scores over the 3 study sessions.

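### The sample size for a paired t-test comes from a normal-quantile formula, so the planned 16 completers give about 75% power, not 80%

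*Protocol article*

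**What the plan says.** Under Null Hypothesis and Sample Size, the protocol article states that "the following paired *t*-test formula was used". In plain notation the formula is n = σ_d² (Z_power + Z_α/2)² / μ_d². Its inputs come from a cited survey of 307 ostomy patients, which "reported a mean of 8.0 (SD 1.7) for the social well-being dimension within the CoH-QOL-Ostomy", and the calculation is made "with 80% power and 95% confidence". The section gives the result as "Our sample size calculation (n=16 for a 15% difference in the dimension of social well-being").

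Table 2 lists N = 35, 16, 4 and 2 for differences of 10%, 15%, 30% and 40% (0.8, 1.2, 2.4 and 3.2 points). The text below it takes a different starting point: "With a sample size calculation of n=4 for 30% difference, we are concerned that our results would lack generalizability". It then goes up to 20, a number that "may help account for a potential 20% attrition rate during recruitment".

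Statistical Analysis fixes the test: "Changes between pre- and postintervention quality of life will be assessed using a dependent" (paired) t-test with a 95% confidence interval.

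**The concern.** A formula in normal quantiles treats the SD of the differences as known. The t-test estimates it on n − 1 degrees of freedom and needs a larger critical value. With hundreds of participants the gap can be ignored. At 16 it costs a few points of power, and at 4 or 2 the approximation breaks down.

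Two things follow for this trial. First, the number of completers the plan allows for is the same 16 that the formula produced, so any shortfall at 16 is a shortfall of the design at its planned attrition. A null result from 16 completers would then be read against a power the study did not have. Second, the reader is given two starting points for the choice of 20 (n=16 for 15%, and n=4 for 30%), and the second rests on a table entry that the t-test does not support.

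**Working it through.** **Inputs (all from the protocol article).** SD 1.7, used as σ_d; power 80%; 95% confidence, two-sided because the formula uses Z_α/2; μ_d = 0.8, 1.2, 2.4 and 3.2; 20 enrolled; 20% attrition; paired t-test.

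**Step 1: reproduce Table 2.** (0.8416 + 1.9600)² = 7.849 and 1.7² = 2.89, so n = 2.89 × 7.849 / μ_d²:

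| μ_d | Formula | Printed N | Rounded up |
|---|---|---|---|
| 0.8 | 35.44 | 35 | 36 |
| 1.2 | 15.75 | 16 | 16 |
| 2.4 | 3.94 | 4 | 4 |
| 3.2 | 2.22 | 2 | 3 |

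The table is reproduced by rounding to the nearest integer, so the 10% and 40% rows are rounded down. Even under the normal approximation those two rows fall short of 80% (79.5% and 75.9%). A one-sided 5% calculation gives 27.9, 12.4, 3.1 and 1.7. It does not reproduce 35 or 16, which confirms that the plan is two-sided.

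**Step 2: power of the test actually planned.** For a paired t-test, power = P(|T| > t_{0.975, n−1}), where T is noncentral t with n − 1 degrees of freedom and noncentrality μ_d√n / 1.7. At n = 16 and μ_d = 1.2 the noncentrality is 1.2 × 4 / 1.7 = 2.824. The normal critical value of 1.960 gives 80.6% power; the t critical value on 15 degrees of freedom is 2.131, and exact power is 75.2%.

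| μ_d | Printed N | Exact power at printed N | Smallest n for 80% |
|---|---|---|---|
| 0.8 | 35 | 77.2% | 38 |
| 1.2 | 16 | 75.2% | 18 |
| 2.4 | 4 | 48.9% | 7 |
| 3.2 | 2 | 16.6% | 5 |

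Simulation with 200,000 replicates per row gave 77.3%, 75.3%, 49.0% and 16.6%.

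**Step 3: the adopted design.** 20 × 0.8 = 16 completers. Power for 1.2 points by number completing:

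| Completers | 16 | 17 | 18 | 19 | 20 |
|---|---|---|---|---|---|
| Power | 75.2% | 78.0% | 80.6% | 82.9% | 84.9% |

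With 16 completers, 80% power is reached at a change of 1.27 points rather than 1.2. To be left with 18 after 20% attrition, enrolment would have to be 18 / 0.8 = 22.5, that is 23.

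**The case against.** The strongest reply is that the effect on the trial is small. This is a pilot, 20 are enrolled, and power is at least 80% for 1.2 points unless three or more drop out. The 20% loss is described only as potential. The choice of SD matters more than the choice between Z and t: 1.7 is a cross-sectional SD, and with equal SDs at both times it equals the SD of differences only if the pre-post correlation is 0.5. The document gives no correlation. Over an assumed range, power at 16 completers is 67% for a correlation of 0.4, 75% for 0.5, 84% for 0.6 and about 93% for 0.7. All of this stands. It lowers the severity and requires a caveat on any restated power, but it does not make the 80% correct on the plan's own inputs.

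A directional hypothesis might suggest a one-sided test, which would give 85.3% at 16. The formula's α/2 and the 95% interval rule that out as the plan's calculation.

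A reader might also infer stronger points that the document does not support:

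- *That rounding down causes the shortfall at 16.* It does not. 15.75 was correctly rounded up, and the loss comes only from using Z instead of t.
- *That the trial has 49% or 17% power.* Those figures belong to n=4 and n=2. The first is mentioned only to be judged too small, and neither is the adopted size.
- *That gains of 2.4 or 3.2 points from a mean of 8.0 are impossible.* That needs a 0 to 10 score range, which the document never states.
- *That the two sample-size passages contradict each other numerically.* Table 2 can be read as a sensitivity table, and 16 / 0.8 = 20 agrees with enrolment. The fault is an unclear rationale.

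**Conclusion.** The point holds, with moderate severity. The formula does not match the planned test. At the 16 completers the plan allows for, power for a 1.2-point change is about 75% against the stated 80%, and 18 completers are needed. The shortfall is about 5 percentage points, or 0.07 points of detectable change, and it disappears if at least 18 of the 20 complete. In Table 2, all four sizes are too small for a t-test, and the 10% and 40% rows are also rounded down. The argument from n=4 rests on an entry that should be 7.

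These figures assume a two-sided 5% test and an SD of paired differences of 1.7, both taken from the plan. The second is an assumption that the document does not support with paired data.

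**What to change.** Keep 20 enrolled and change the text and one table:

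1. State the power as: about 75% for a 1.2-point change if 16 complete, 81% if 18 complete and 85% if all 20 complete; 80% power for about 1.27 points with 16. Add that this is two-sided at 5% and assumes an SD of paired differences of 1.7, taken from a cross-sectional SD.
2. Recompute Table 2 with the noncentral t distribution (38, 18, 7 and 5), or recompute the first two rows and drop the last two. Dropping them is an editorial choice.
3. Make the 15% (1.2-point) target with 20% attrition the single stated basis for 20, in place of the argument from n=4.

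The cost is a slightly less favourable stated power. Enrolment, endpoint and analysis do not change. If the authors would rather guarantee 80% after 20% attrition, the price is three more participants (23 in place of 20), but the point does not require it.

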**Figure 1 figure1:**
[figure not shown]
Screenshots from the Ostom-i patient app showing status, hydration, and graph.

**Figure 2 figure2:**
[figure not shown]
Screenshot from the Ostom-i patient app showing user interface, status, hydration, and graph.

**Figure 3 figure3:**
[figure not shown]
Participant flowchart. QOL-Ostomy: Quality of Life Questionnaire for a Patient with an Ostomy.

**Table 1 table1:** City of Hope quality of life dimension definitions obtained from Gemmill et al [22].

Dimension	Definition
Physical well-being	Physical symptoms and functional ability
Psychological well-being	Emotional components of the illness including positive as well as negative aspects
Social well-being	Role of the patient with the family and society including occupational, sexual, and personal relationships
Spiritual well-being	Religious aspects and existential concerns

**Table 2 table2:** Desired sample size number (N) based on % difference.

% Difference	Absolute change in dimension of well-being (μd)	Sample size (N)
10	0.8	35
15	1.2	16
30	2.4	4
40	3.2	2

Furthermore, Gemmill et al [22] report a lower SD for the dimension of social well-being (SD 1.7) as compared to physical well-being (SD 1.8), psychological well-being (SD 1.9), and spiritual well-being (SD 2.3). Thus, we chose to base our sample size calculation on the dimension of social well-being. With a sample size calculation of n=4 for 30% difference, we are concerned that our results would lack generalizability. Therefore, by increasing our sample size to 20, we hope that our results will be more generalizable and may help account for a potential 20% attrition rate during recruitment (Table 2).

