### Data Collection, Management, and Analysis

#### Primary Outcome Data Collection Methods

Our primary outcome, change in ostomy-specific, health-related quality of life from baseline, will be measured using the modified CoH-QOL-Ostomy. This survey was designed and studied for reliability and validity by Grant et al [14] with an overall questionnaire alpha of .95, suggesting strong consistency. The survey can be divided into 6 sections: 1) social adjustment to ostomy (coefficient alpha=.90, correlation to single quality of life item: *r*=.44, *P*>.001); 2) general quality of psychological well-being (coefficient alpha=.83, correlation to single quality of life item: *r*=.76, *P*>.001); 3) general quality of physical well-being (coefficient alpha=.88, correlation to single quality of life item: *r*=.39, *P*>.001); 4) disease-specific effects on physical well-being (coefficient alpha=.77, correlation to single quality of life item: *r*=.24, *P*>.001); 5) general quality of spiritual well-being (coefficient alpha=.81, correlation to single quality of life item: *r*=.51, *P*>.001); and 6) disease specific effects on psychological well-being (coefficient alpha=.82, correlation to single quality of life item: *r*=.38, *P*>.001) [14]. This validated survey has successfully been used by number of studies examining ostomy-related quality of life [22-27].

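### The sample size is calculated for the social well-being dimension, but the primary outcome is the overall 43-item CoH-QOL-Ostomy score, so the stated n=16 and 80% power are unsupported for the primary test

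*Protocol article*

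**What the plan says.** The outcome is fixed in three places in the protocol article.

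- Primary Outcome Data Collection Methods: "Our primary outcome, change in ostomy-specific, health-related quality of life from baseline, will be measured using the modified CoH-QOL-Ostomy".
- Primary Outcome Measures, on scoring: "Ostomy-specific, health-related quality of life is calculated by summing scores for each question then dividing by the total number of questions (ie, 43 questions"). The four dimensions are scored separately, each over its own items.
- Null Hypothesis and Sample Size: the null is that "there will be no improvement in ostomy-specific, health-related quality of life as measured by the CoH-QOL-Ostomy, compared to baseline measurements prior to sensor use". The calculation is presented as the one that tests this null.

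The inputs to that calculation belong to one dimension. The cited study of 307 ostomy patients "reported a mean of 8.0 (SD 1.7) for the social well-being dimension within the CoH-QOL-Ostomy, with 80% power and 95% confidence". The result is n=16 for a 15% difference, which Table 2 gives as 1.2 points. Two reasons are offered for the choice. The first is that the same study is one "who reported social well-being to have a higher mean (8.0) than overall quality of life (mean 7.7"). The second, after Table 2, is that the SD of social well-being (1.7) is below those of physical (1.8), psychological (1.9) and spiritual well-being (2.3). The text then concludes: "Thus, we chose to base our sample size calculation on the dimension of social well-being". The planned N is 20, partly to allow for 20% attrition.

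**The concern.** The variable that was sized is not the variable that will be tested. Social well-being is nowhere named as the primary endpoint, and no calculation is given for the overall score.

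The reasons for the choice do not bridge the gap. When the effect is set as a percentage of the mean, a higher mean turns the same percentage into more points, and a lower SD reduces n directly. Both features make the required sample smaller. Neither shows that social well-being stands in for the overall score, or that it is where the sensor should act. The overall mean was at hand and was not used.

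At stake is the reading of the result. If the overall score shows no significant change, there is no planned detectable change on that score to set the result against. Because the only powered quantity is one dimension, the report could also drift towards that dimension after the fact.

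**Working it through.** **Inputs from the article.** Social well-being mean 8.0, SD 1.7; overall quality of life mean 7.7, no SD given; 80% power; two-sided 5% level (95% confidence and Z for α/2 in the formula); planned N=20; 20% attrition, so 20 × 0.8 = 16 completers; paired *t*-test as the analysis.

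**Formula.** n = σ_d² (Z_power + Z_α/2)² / μ_d², with (0.8416 + 1.96)² = 7.849.

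**1. The plan's own figure.** μ_d = 0.15 × 8.0 = 1.2. Then n = 1.7² × 7.849 / 1.2² = 22.68 / 1.44 = 15.75, which rounds up to 16. The stated n=16 is reproduced. The other rows of Table 2 follow in the same way: 35.4, 3.9 and 2.2 against the printed 35, 4 and 2.

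**2. Change only the mean.** Take 7.7 as the mean of the overall score and keep σ_d = 1.7 as an assumption. μ_d = 0.15 × 7.7 = 1.155. Then n = 22.68 / 1.334 = 17.0 (17.004, so 18 when rounded up).

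**3. Power, like for like.** The normal approximation and the exact paired *t* (noncentral *t*) must be kept apart.

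| Inputs (σ_d = 1.7) | Normal, n=16 | Exact *t*, n=16 | Exact *t*, n=20 |
|---|---|---|---|
| Social well-being, μ_d = 1.2 | 80.6% | 75.2% | 84.9% |
| Overall score, μ_d = 1.155 | 77.6% | 71.9% | 82.2% |

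On either scale the change of mean costs about 3 points at n=16. The remaining distance from 80% to 72% comes from the normal approximation, and it affects the plan's own inputs as well.

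**4. Range for the missing SD.** With μ_d = 1.155 and an assumed SD of change:

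| Assumed SD of change | n by the plan's formula | Exact power, 16 completers | Exact power, 20 completers |
|---|---|---|---|
| 1.5 | 13.2 | 82% | 90% |
| 1.6 | 15.1 | 77% | 86% |
| 1.7 | 17.0 | 72% | 82% |
| 1.8 | 19.1 | 67% | 78% |
| 1.9 | 21.2 | 62% | 73% |

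**5. Which SD the formula needs.** σ_d is the SD of within-patient change. The 1.7 is reported alongside the mean as the SD of scores across patients. If the SD is the same before and after, σ_d = SD × √(2(1 − ρ)), where ρ is the pre-post correlation, so the two are equal only at ρ = 0.5. With a score SD of 1.7 and μ_d = 1.155, ρ = 0.3 gives σ_d = 2.01, n = 23.8 and exact power of 57% at 16 completers. With ρ = 0.7, σ_d = 1.32, n = 10.2 and power is 91%.

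**6. Detectable change.** The paired *t*-test has 80% power for 0.749 SD of change at n=16 and 0.660 at n=20. At an assumed SD of change of 1.7 these are 0.749 × 1.7 = 1.27 points and 0.660 × 1.7 = 1.12 points.

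**The case against.** The strongest reply is that the mismatch may be harmless or even conservative. If the 43 items divide among the four dimensions, the overall score is a weighted average of the dimension scores, and its SD cannot exceed the weighted average of theirs. With equal weights (an assumption, since item counts per dimension are not given) the ceiling is (1.7 + 1.8 + 1.9 + 2.3) / 4 = 1.925, reached only if the dimensions correlate perfectly. At a common correlation of 0.5 between dimensions the SD is about 1.52, the formula gives n = 13.7, and exact power at 16 is 81%. This stands. A reader might infer from the mismatch that the trial is underpowered, or apply the spiritual dimension's SD of 2.3 to the overall score. The article supports neither.

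Three further points also stand.

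- The planned N of 20 covers the base case: 82% if all 20 complete.
- A reader might take social well-being to have the highest mean of the dimensions, or the most favourable figures of all. The article shows only that its mean exceeds that of overall quality of life and that its SD is the lowest of the four dimensions. The other dimension means and the overall SD are not given.
- The article does not say how the 7.7 was scored, and it mentions a single quality-of-life item elsewhere. Treating 7.7 as the mean of the 43-item score is an assumption.

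It can also be said that this is a single-group pilot that openly labels its calculation as one for social well-being. That bears on severity but does not remove the defect: the article ties the calculation to a formal null hypothesis on a different score and attaches 80% power to it. Nor is this a detail left to a fuller document, since the inputs and the rationale are all stated.

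**Conclusion.** The point holds as a mismatch between the variable sized and the variable tested. The stated n=16 and 80% power belong to social well-being and are unsupported for the primary test on the overall score. The reasons given for the choice both reduce n and do not justify it.

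The demonstrable effect is small: about 3 points of power at 16 completers, and 17.0 instead of 15.8 by the plan's formula. This rests on 7.7 being the mean of the 43-item score, a 15% change being the target, and an SD of change of 1.7. Over assumed SDs of change from 1.5 to 1.9, exact power runs from 82% to 62% at 16 completers and from 90% to 73% at 20. Adequate and inadequate power both lie within that range, so the article leaves the question open. The pre-post correlation, which is not stated, matters more than the choice of mean. This should be fixed, but it does not undermine the planned N.

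**What to change.** Keep N=20. Restate the sample size paragraph and Table 2 for the overall 43-item score, as follows:

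- state an absolute change on that score and justify it as meaningful, in place of a percentage of a dimension mean;
- use the SD of within-patient change, or a score SD converted with a stated pre-post correlation and shown over a range; the between-patient SD of the overall score should not be put into the formula as it stands, since that would repeat the problem in step 5;
- report the change detectable with 80% power by the paired *t*-test: 0.75 SD of change at 16 completers and 0.66 at 20;
- drop the higher mean and lower SD of social well-being as reasons.

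The cost is one paragraph and one table. No patient, test or endpoint changes. The stated power may come out less favourable or more favourable than 80%, depending on the SD of change.
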